### 5.4 Outcome definitions

#### **Primary outcome**

Reported days of methamphetamine use: The primary outcome is change in self-reported days of methamphetamine use in the past 4 weeks from baseline to weeks 4,8,12 and 20, assessed using the Timeline Followback (TLFB)[17], with week 12 being the primary endpoint.

Days when a participant is incarcerated or in hospital (inpatient only) are censored from the TLFB. The length of each assessment window can vary dependent on the actual follow-up date. For this reason an offset term will be included in the model to adjust for variation in the days observed in each assessment window.

TLFB data will be validated against biologically verified abstinence from methamphetamine use contained in oral fluid samples. Data on methamphetamine use from oral fluid samples was not complete at the time of writing this statistical analysis plan.

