$$r = (\text{days of use at follow-up} / \text{days of exposure at follow-up}) / (\text{days of use at baseline} / \text{days of exposure at baseline})$$

$r_p = r$  in placebo group

$r_a = r$  in active group

The interaction coefficient representing the treatment effect is the rate ratio (rr) of these two parameters, i.e.,  $r_a/r_p$ .

Thus, the interaction term can be interpreted as the relative difference in the rate of *change* between the intervention and control groups, which allows for random misbalance at baseline rather than assuming baseline methamphetamine use is the same in both groups.

*Analysis of the primary outcome at week 20:* A separate analysis will be conducted to compare days of methamphetamine use in the past 4 weeks at the week 20 assessment. We have chosen to analyse the week 20 endpoint separately because we believe that (a) differences in the conduct of the week 20 assessment may impact data variability (e.g., phone interviews and greater attrition), and (b) there are differences in the clinical interpretation of the outcome at the week 20 assessment (because

participants are no longer on the trial intervention and are offered off-label mirtazapine and other substance use treatment prior to week 20). We will test the main effect of the trial medication on days of methamphetamine use at week 20 using a mixed model with a group (placebo [0] vs. mirtazapine [1]) by time (baseline [0], week 20 [1]) interaction effect. A negative binomial generalised linear mixed model will be used to test this effect. An exposure term (i.e. offset) will be included in the model to adjust for the exact number of days in each of these periods if the observed number of days in the TLFB varies from 28 days. As noted under the general principles, a random intercept term will be included in the model to account for clustering on repeats [31], and a random intercept term will be included in the model to account for site only if this significantly improves model fit (based on a likelihood ratio test;  $p < 0.05$ ).

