### 6.3 Planned analysis of the secondary outcomes

The analysis of the secondary endpoints will be based on the intention-to-treat dataset and based on unimputed data. All tests will be two-sided with  $p < 0.05$ .

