#### **Depression**

The effect of mirtazapine on depression will be tested using a mixed model using a group (placebo [0] vs. mirtazapine [1]) by time (baseline [0] vs. weeks 4 [1], week 8 [2], week 12 [3]) interaction, with time entered as a factor variable, producing individual effect estimates for each time point and making no assumptions about the linearity of changes over time. The primary timepoint for this endpoint is week 12. A generalised linear mixed model will be used to test this effect.

The effect of mirtazapine on depression at week 20 will be tested using a separate analysis. We will test the main effect of the trial medication on depression at week 20 using a mixed model with a group (placebo [0] vs. mirtazapine [1]) by time (baseline [0], week 20 [1]) interaction effect. A generalised linear mixed model will be used to test this effect. We have chosen to analyse the week 20 endpoint separately because we believe that (a) differences in the conduct of the week 20 assessment may impact data variability (e.g., phone interviews and greater attrition), and (b) there are differences in the clinical interpretation of the outcome at the week 20 assessment (because participants are no longer on the trial intervention and are offered off-label mirtazapine and other substance use treatment prior to week 20).

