## 6.4 Planned analysis of the tertiary and exploratory outcomes

Planned analyses of the tertiary outcomes of other substance use, anxiety, and patient impression will be based on the unimputed intention-to-treat dataset.

Other substance use: The effect of the trial medication on days of other substance use will be tested using a mixed model with a group (placebo [0] vs. mirtazapine [1]) by time (baseline [0], week 4 [1], week 8 [2], week 12 [3], week 20 [4]) interaction effect, with time entered as a factor variable, producing individual effect estimates for each time point and making no assumptions about the linearity of changes over time. The primary timepoint is week 12. A generalised linear mixed model will be used to test this effect.

Anxiety: The effect of mirtazapine on anxiety will be tested using a mixed model using a group (placebo [0] vs. mirtazapine [1]) by time (baseline [0] vs. weeks 4 [1], week 8 [2] and 12 [3]) interaction effect, with time entered as a factor variable, producing individual effect estimates for each time point and making no assumptions about the linearity of changes over time. The primary timepoint is week 12. A generalised linear mixed model will be used to test this effect.

Patient impression: The effect of mirtazapine on the PGI scale score will be tested a group contrast (placebo [0] vs. mirtazapine [1]) across all follow-up time points (weeks 4, 8 and 12) to obtain an average treatment effect across the 12-week intervention period. A generalised linear mixed model will be used to test this effect.

Adverse events: The analysis of adverse event data will be based on the safety dataset and include only adverse event data for the 12-week trial medication period (wk 0 to wk 12). The percentage of participants reporting adverse events and serious adverse events for each System Organ Class will be compared between conditions using a Pearson's Chi-Square test. For serious adverse events, expectedness and causality will be reported.

Suicidality: The analysis of suicidality will be based on the safety dataset and include only suicidality data for the 12-week trial medication period (wk 0 to wk 12). The percentage of participants who screened positive for suicide risk (CSSRS-S score of 3 or greater) during the 12-week trial medication period (wk 0 to wk 12) will be compared between conditions (placebo [0] vs. mirtazapine [1]) using a Pearson's Chi-Square test.

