## 6.5 Sensitivity analyses

Sensitivity analyses will be conducted that imputes missing data for the analyses of the primary outcome of methamphetamine use days and for the secondary outcome of methamphetamine abstinence.

Sensitivity analysis may be conducted to test the assumption that the data are not missing at random for the primary outcome of methamphetamine use days and for the secondary outcome of methamphetamine abstinence. This will involve testing the impact of different assumed outcome values for missing data on the final treatment effect estimate.

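### The main week-20 estimates for methamphetamine days and PHQ-9 omit the week 4, 8 and 12 data, so they allow for dropout through arm and baseline only

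*Combined protocol and SAP*

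**What the plan says.** Section 5.4 defines the primary outcome as "change in self-reported days of methamphetamine use in the past 4 weeks from baseline to weeks 4,8,12 and 20", with week 12 as the primary endpoint. PHQ-9 has the same visits and the same primary timepoint.

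The week-12 estimates come from a four-visit mixed model. Week 20 is handled apart. For days of use, section 6.2 plans a negative binomial mixed model "using a mixed model with a group (placebo [0] vs. mirtazapine [1]) by time (baseline [0], week 20 [1]) interaction effect". For PHQ-9, section 6.3 (Depression) says "The effect of mirtazapine on depression at week 20 will be tested using a separate analysis" and codes time in the same two levels.

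Two reasons are given for the separation. One is that "differences in the conduct of the week 20 assessment may impact data variability (e.g., phone interviews and greater attrition". The other is that the outcome means something different once participants are off trial medication and have been offered other treatment.

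On missing data:

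- Section 6.3 states: "The analysis of the secondary endpoints will be based on the intention-to-treat dataset and based on unimputed data". Section 6.2 says the same of the primary outcome.
- Section 6.5 states: "Sensitivity analyses will be conducted that imputes missing data for the analyses of the primary outcome of methamphetamine use days", and adds abstinence. PHQ-9 is not named. An analysis under not-missing-at-random assumptions is optional and covers the same two outcomes.
- Section 6.8 puts baseline and any observed follow-up days of use into the imputation model. The fallback, inverse probability of censoring weighting, adjusts for baseline variables.

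For other substance use, section 6.4 keeps all visits in one model: "week 12 [3], week 20 [4]) interaction effect, with time entered as a factor variable".

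**The concern.** In an unimputed analysis, the mixed model itself is what deals with missing outcomes. It does so by using each participant's other observed visits. With only a baseline row and a week-20 row, nothing seen on treatment can inform the missing week-20 value.

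If participants who are using heavily or still depressed at week 12 are lost at a different rate in one arm than in the other, the week-20 contrast is biased although data that would correct it are in hand. If dropout is completely random there is no bias, but some precision is given up.

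Neither stated reason calls for dropping these rows. A different clinical meaning after treatment is a reason to report a separate contrast, and time as a factor already gives one. Different variability at week 20 can be met through the variance estimate. Greater attrition is a reason to keep the earlier visits. Section 6.4 does keep them for other substance use, which the Appendix lists in the same week-20 phone assessment.

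**Working it through.** **Data left out.** From Table 3, with 339 treated:

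- Week 4: 315/339 = 93%.
- Week 8: 300/339 = 88.5% (printed as 89%).
- Week 12: 293/339 = 86%.
- Any assessment after baseline (section 4.2): 339 - 20 = 319.

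**The plan's own attrition figure.** Section 3.3: 340 x (1 - 0.25) = 255, as stated. This is for week 12. The plan gives no figure for week 20, and those data were incomplete when the SAP was written. The week-20 attrition rate, the correlations and the dropout mechanism below are therefore assumptions.

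**How much the earlier visits can help.** Suppose 25% are missing at week 20 and dropout is monotone. From Table 3, about 14 of those 25 points (100 - 86) have no week-12 value, and about 7 (100 - 93) have baseline only. A five-visit model has nothing extra to use for that last group.

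**Check 1: large-sample bias, in SD units.** 100,000 per arm, linear outcome, weeks 4-12 complete; week-20 missingness 20% or 30% and driven by the week-12 value (log-odds 1 per SD); correlation exchangeable at 0.4 or 0.6, or decaying.

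| Dropout mechanism | Baseline + week 20 only | All five visits |
|---|---|---|
| Same in both arms | 0.00 to 0.02 | about 0.00 to 0.01 |
| Depends on week 12 in one arm only | 0.04 to 0.10 | within about 0.005 |
| Opposite directions in the two arms | 0.08 to 0.19 | within about 0.006 |

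The standard error of the contrast at N = 339 would be about 0.11 to 0.14 SD. For PHQ-9, the baseline interquartile range of 4 to 13 gives SD = 9/1.349 = 6.7 if roughly normal. The one-arm case is then 0.04 x 6.7 = 0.3 to 0.10 x 6.7 = 0.7 points. The opposite-direction case reaches 0.19 x 6.7 = 1.3 points.

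**Check 2: trial-sized simulation on the scale of days.** N = 339; effect 4.1 days (ratio 0.75); SD 9.5 days; correlation 0.45 between baseline and week 20, and 0.72 between week 12 and week 20.

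- Weeks 4-12 observed for everyone: the two-row bias was 4-7% of the effect under a common mechanism (odds ratio 2-3 per SD) and 9-20% under a one-arm mechanism (odds ratio 1.5-2). The bias was upward or downward according to the arm. Under random dropout the standard error was 1.209 days for two rows and 1.167 for the joint model, a saving of 1 - 1.167/1.209 = 3.5%. These figures flatter the joint model, because they ignore Table 3.
- With the Table 3 pattern imposed: two-row bias about 1-2% under a common mechanism and about 10% under a one-arm mechanism; precision gain about 2-3%. Keeping weeks 4-12 removed most of the bias.

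In days, 10% of 4.1 is 0.41. Against a standard error of 1.209 that is 0.41/1.209 = 0.34 standard errors. Nominal 95% coverage becomes Φ(1.96 - 0.34) - Φ(-1.96 - 0.34) = 0.947 - 0.011, or about 94%. A 2% bias is 0.08 days, or 0.07 standard errors, and leaves coverage unchanged to the nearest percent.

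**Check 3: the standard error of the five-visit model.** A random intercept with only a visit-specific residual reported a week-20 standard error of about 1.0, against an empirical 1.1-1.2. That is roughly 10-17% too small. Robust errors gave 1.15-1.17, about right.

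**The case against.** The separation is pre-specified and reasoned, and keeping a post-treatment phone assessment apart from the on-treatment visits is defensible. Week 20 is not the primary timepoint for either outcome. The larger biases need a dropout mechanism that differs by arm, and no figure in the documents shows one. The simulated effect also assumes that a ratio of 0.75 persists after trial medication stops. All of this stands and limits the weight of the point. It supports a separate week-20 contrast; it does not support removing weeks 4-12 from the model that estimates it.

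A reader might infer that informative dropout at week 20 goes wholly uncorrected. For days of use the documents do not support that. Section 6.5 commits to an imputed analysis of the primary outcome, section 5.4 includes week 20 in that outcome, and section 6.8 uses observed follow-up days of use as predictors. The gap for days of use is that week 20 is not named and that the imputed result is only a sensitivity analysis. For PHQ-9 the gap is complete.

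A reader might also infer that weeks 4-12 are known to be the best predictors of who is missing at week 20. That is plausible, but nothing in the documents shows it. Section 4.4 records 56 participants who chose to stop medication, with side-effects among the reasons. Dropout that differs by arm is therefore conceivable, not demonstrated.

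**Conclusion.** The concern holds in limited form. The main week-20 estimates for days of use and PHQ-9 rest on missing at random given arm and baseline alone. The likely cost is modest: about 1-2% of the effect under a common dropout mechanism, about 10% (0.41 days, a third of a standard error) under a one-arm mechanism, and 2-3% of interval width. These figures depend on the assumed correlations, an assumed week-20 attrition near 25%, a normal approximation to days of use, and data missing at random given the observed visits.

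The documents do not support reading this as a threat to the trial's main result: the week-12 model keeps all its visits and is untouched. The change is still worth making, because the two-row model offers little beyond simplicity, PHQ-9 at week 20 has no specified safeguard, and section 6.4 already uses the alternative.

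**What to change.** In 6.2 (week 20) and 6.3 (Depression), estimate the week-20 effect from a model that keeps the week 4, 8 and 12 rows:

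- Enter time as a five-level factor (baseline, weeks 4, 8, 12, 20), with the offset for days of use.
- Require participant-clustered robust or bootstrap standard errors or, for PHQ-9, an unstructured covariance. A random intercept with only a visit-specific residual is not enough (Check 3).
- Report only the group-by-week-20 contrast from this model. Leave the week-12 model unchanged, and keep the two-row model as a sensitivity analysis.

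Equivalently, state in 6.5 and 6.8 that multiple imputation covers week 20 for both days of use and PHQ-9, with weeks 4, 8 and 12 as predictors, and let any inverse probability weighting use post-baseline data.

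The cost is a change to a few SAP paragraphs and one slightly larger model per outcome (or a wider imputation model), with no new data. The choice should be fixed before unblinding, since section 6.1 allows models to be modified afterwards on grounds of fit.

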### 6.3 Planned analysis of the secondary outcomes

The analysis of the secondary endpoints will be based on the intention-to-treat dataset and based on unimputed data. All tests will be two-sided with  $p < 0.05$ .

#### **Abstinence (negative oral fluid samples)**

Descriptive data on the proportion of negative oral fluid samples in each group across the active trial phase will be presented. The effect of mirtazapine on methamphetamine negative oral fluid samples (no [0], yes [1]) will be tested using a group contrast (placebo [0] vs. mirtazapine [1]) across all follow-up time points (weeks 4, 8 and 12) to obtain an average treatment effect across the 12-week intervention period. A generalised linear mixed model with a logistic link will be used to test this effect.

#### **Depression**

The effect of mirtazapine on depression will be tested using a mixed model using a group (placebo [0] vs. mirtazapine [1]) by time (baseline [0] vs. weeks 4 [1], week 8 [2], week 12 [3]) interaction, with time entered as a factor variable, producing individual effect estimates for each time point and making no assumptions about the linearity of changes over time. The primary timepoint for this endpoint is week 12. A generalised linear mixed model will be used to test this effect.

The effect of mirtazapine on depression at week 20 will be tested using a separate analysis. We will test the main effect of the trial medication on depression at week 20 using a mixed model with a group (placebo [0] vs. mirtazapine [1]) by time (baseline [0], week 20 [1]) interaction effect. A generalised linear mixed model will be used to test this effect. We have chosen to analyse the week 20 endpoint separately because we believe that (a) differences in the conduct of the week 20 assessment may impact data variability (e.g., phone interviews and greater attrition), and (b) there are differences in the clinical interpretation of the outcome at the week 20 assessment (because participants are no longer on the trial intervention and are offered off-label mirtazapine and other substance use treatment prior to week 20).

#### **Other secondary endpoints (sleep, quality of life and HIV risk)**

The effect of mirtazapine on other secondary endpoints (sleep, quality of life and HIV risk) will be tested with a mixed model using a group (placebo [0] vs. mirtazapine [1]) by time (baseline [0] vs. weeks 4 [1], week 8 [2] and 12 [3]) interaction, with time entered as a factor variable, producing individual effect estimates for each time point and making no assumptions about the linearity of

changes over time. The primary timepoint for these endpoints is week 12. A generalised linear mixed model will be used to test these effects.

## 6.4 Planned analysis of the tertiary and exploratory outcomes

Planned analyses of the tertiary outcomes of other substance use, anxiety, and patient impression will be based on the unimputed intention-to-treat dataset.

Other substance use: The effect of the trial medication on days of other substance use will be tested using a mixed model with a group (placebo [0] vs. mirtazapine [1]) by time (baseline [0], week 4 [1], week 8 [2], week 12 [3], week 20 [4]) interaction effect, with time entered as a factor variable, producing individual effect estimates for each time point and making no assumptions about the linearity of changes over time. The primary timepoint is week 12. A generalised linear mixed model will be used to test this effect.

Anxiety: The effect of mirtazapine on anxiety will be tested using a mixed model using a group (placebo [0] vs. mirtazapine [1]) by time (baseline [0] vs. weeks 4 [1], week 8 [2] and 12 [3]) interaction effect, with time entered as a factor variable, producing individual effect estimates for each time point and making no assumptions about the linearity of changes over time. The primary timepoint is week 12. A generalised linear mixed model will be used to test this effect.

Patient impression: The effect of mirtazapine on the PGI scale score will be tested a group contrast (placebo [0] vs. mirtazapine [1]) across all follow-up time points (weeks 4, 8 and 12) to obtain an average treatment effect across the 12-week intervention period. A generalised linear mixed model will be used to test this effect.

Adverse events: The analysis of adverse event data will be based on the safety dataset and include only adverse event data for the 12-week trial medication period (wk 0 to wk 12). The percentage of participants reporting adverse events and serious adverse events for each System Organ Class will be compared between conditions using a Pearson's Chi-Square test. For serious adverse events, expectedness and causality will be reported.

Suicidality: The analysis of suicidality will be based on the safety dataset and include only suicidality data for the 12-week trial medication period (wk 0 to wk 12). The percentage of participants who screened positive for suicide risk (CSSRS-S score of 3 or greater) during the 12-week trial medication period (wk 0 to wk 12) will be compared between conditions (placebo [0] vs. mirtazapine [1]) using a Pearson's Chi-Square test.

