#### 4.4 Medication discontinuation

Of the 339 participants who attended their baseline assessment and received the trial medication, 85 participants were permanently discontinued from the 30 mg trial medication. (Note. Participants who did not receive or stopped taking the 15 mg taper dose were not recorded as medication discontinuations under the study protocol.)

- 14 participants were discontinued from the medication by the study team (e.g., due to adverse reactions or other medical risks).
- 56 participants chose to stop the medication (e.g., because they did not like the side-effects or no longer wanted to participate in the study).
- 15 participants ceased medication due to circumstantial factors (e.g., incarceration, loss to follow-up, being withdrawn from the study).

Participants who discontinued the trial medication included 20 participants who were withdrawn from the study prior to week 12 (Figure 1). The remaining 65 participants who were discontinued from the study medication were followed up for study assessments.

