## Outcomes for which there are no planned analyses

Treatment satisfaction: Scores on the Treatment Satisfaction Questionnaire for Medication Version II (TSQM II) [27] at week 12 are being used to assess treatment satisfaction. The TSQM II provides a global satisfaction summary score and subscale scores for medication convenience, side-effects, and effectiveness. Additional unpublished questions have been included at other weeks to assess tolerability and expected reactions to mirtazapine (see Appendix for details).

Concomitant medications: All medications taken by participants during the trial are recorded on a template adapted from the National Institute of Health Concomitant Medications Form [28]. For each medication is coded against the WHO generic medication code and information is recorded on the dose, frequency and route.

Health Economics: Health economics data collected include: the EuroQol 5D – 5L [22] at baseline and weeks 4, 8 and 12; the Work Productivity and Activity Impairment Questionnaire – General Health (WPAIQ-GH) V2 [29] at week 12; and, contact with health services and the criminal justice system in the three months prior to baseline and from baseline to the week 12 assessment (collected at the week 12 assessment).

Adverse events (AEs): The percentage of participants reporting AEs, and serious adverse events (SAEs), by System Organ Classification, will be coded according to the Medical Dictionary for Regulatory Activities (MedDRA)[30]. AEs will be counted once only for a given participant.

Body Mass Index (BMI): BMI based on verified weight and height at eligibility and the final medical assessment.

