#### **Exploratory outcomes:**

5. *Adverse events (AEs):* Adverse events were assessed using open ended prompts about problems with the participant's health and problems with the study medication. All AEs were logged using a structured form that included information on date of onset and completion, severity, treatment received, relatedness to the trial medication, and whether the AE was a serious AE (SAE). AEs were assessed at week 2 after starting the trial medication; AEs were reviewed and updated at each assessment thereafter. AEs also include events that were identified outside this assessment process (e.g., at medical assessments) with these recorded at the nearest completed assessment. All AEs were coded by system organ classification according to the Medical Dictionary for Regulatory Activities (MedDRA)[30]
6. *Height and weight:* Self-reported height and weight were recorded at the week 12 assessment. Actual height and weight were re-assessed at the final medical assessment (week 18) when this was done in person.
7. *Treatment satisfaction* was assessed at week 12 using Treatment Satisfaction Questionnaire for Medication Version II (TSQM II) [27] which assesses medication convenience, side-effects and effectiveness for the previous 2-3 weeks (or since the participant had last used the medication, if

they had ceased medication). The TSQM II provides a global satisfaction summary score and subscale scores for medication convenience, side-effects, and effectiveness.

*Unpublished questions on medication tolerability:* Additional questions were included at weeks 4 and 8 to assess medication tolerability and adverse reactions to mirtazapine. These included a set of 5 generic questions about participants' perceived medication impacts and 7 questions specific to the expected effects of mirtazapine. These questions did not have a timeframe (they rated the participant's current beliefs and attitudes). At week 2 and week 16 a single question was included asking participants whether they had experienced any adverse reactions to mirtazapine, and withdrawal effects from ceasing mirtazapine, respectively. A final question asked participants whether the participant thought they were receiving the placebo (dummy pill) or active medication (mirtazapine) with the options of don't know, placebo (dummy pill), active medication (mirtazapine).

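### Adverse events are compared between arms only by System Organ Class, with no pre-specified summary by arm of specific events or severity, and the expected-effect questions have no planned analysis

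*Combined protocol and SAP*

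**What the plan says.** **Planned comparison.** SAP section 6.4 (Adverse events) uses the safety dataset for weeks 0 to 12 and a Pearson chi-square test: "The percentage of participants reporting adverse events and serious adverse events for each System Organ Class will be compared between conditions". Expectedness and causality are reported for serious events only. Suicidality (CSSRS-S score of 3 or more) is compared separately. Sections 6.5 to 6.7 add no safety analysis.

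**What was collected.** The Appendix (Exploratory outcomes) explains that "Adverse events were assessed using open ended prompts about problems with the participant's health and problems with the study medication". Each event was logged with its dates, severity, treatment, relatedness and seriousness, and was coded by MedDRA system organ class. The Appendix also describes additional questions at weeks 4 and 8, among them "7 questions specific to the expected effects of mirtazapine".

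**Where those questions stand.** Section 5.4 places them under the heading for outcomes with no planned analyses: "Additional unpublished questions have been included at other weeks to assess tolerability and expected reactions to mirtazapine".

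**Stopping medication.** Section 4.4 reports 85 permanent discontinuations among 339 treated: 14 by the study team, 56 by participant choice and 15 for circumstantial reasons. Side-effects are one of the example reasons: "56 participants chose to stop the medication (e.g., because they did not like the side-effects". Section 5.3 commits to reporting the number discontinued, but does not say by arm or by reason.

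**The concern.** The objective in section 2.2 names safety alongside effectiveness. A participant enters a class percentage in the same way whether the event is a recognised drug reaction or an unrelated complaint in the same body system. The planned output therefore shows whether a body system differed. It does not show which reaction caused the difference, or whether it was mild or severe.

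Two things are at stake. First, a specific reaction can be masked by background events in its class. Second, the SAP was written on blinded data (section 6.1). If event-level tables are chosen after unblinding, the choice of which reactions to show is no longer protected by pre-specification.

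**Working it through.** **1. Reading the sections together.** Section 6.4 fixes the level of comparison at System Organ Class. The Appendix shows that severity and relatedness exist for every event, but 6.4 uses neither for non-serious events. Section 5.4 leaves the expected-effect questions unanalysed, and nothing in 6.4 to 6.7 takes them up. The gap is therefore there on the face of the SAP. Section 5.4 also lists adverse events themselves under its no-planned-analysis heading although 6.4 plans a comparison; the two sections need reconciling.

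**2. Number per arm.** The SAP gives no adverse-event rate, class frequency or power to reproduce. Section 4.2 reports 339 treated, of whom 20 attended no assessment after baseline: 339 − 20 = 319, or 159.5 per arm if split evenly. I take 160. The safety dataset requires an assessment at week 4, 8 or 12, so this is approximate.

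**3. Formulas.** Let p be the rate of a specific reaction and b the share of participants, equal in both arms, with an unrelated event in the same class. If the two are independent, the class rate is q = 1 − (1 − p)(1 − b). The difference between arms then shrinks by the factor (1 − b). Two-sided 5% power by normal approximation is Φ[(d − 1.96·se0)/se1], where d is the difference, se0 = √(2·q̄(1 − q̄)/n) and se1 = √((q0(1 − q0) + q1(1 − q1))/n).

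**4. Worked cases, n = 160 per arm, assumed reaction rates 10% and 25%.**
- b = 0: se0 = √(2 × 0.175 × 0.825/160) = 0.0425 and se1 = √((0.09 + 0.1875)/160) = 0.0416, so power = Φ[(0.15 − 0.0833)/0.0416] ≈ 0.945.
- b = 20%: rates are 28% and 40%, se0 = 0.0530 and se1 = 0.0525, so power = Φ[(0.12 − 0.1038)/0.0525] ≈ 0.62.

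| Background b | Class rates | Difference (points) | Power |
|---|---|---|---|
| 0% | 10.0% vs 25.0% | 15.0 | 0.945 |
| 5% | 14.5% vs 28.75% | 14.25 | 0.88 |
| 10% | 19.0% vs 32.5% | 13.5 | 0.79 |
| 20% | 28.0% vs 40.0% | 12.0 | 0.62 |
| 30% | 37.0% vs 47.5% | 10.5 | 0.48 |
| 40% | 46.0% vs 55.0% | 9.0 | 0.36 |

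**5. Other assumed rates.** For 10% vs 20%, power is about 71% alone and 47%, 33%, 25% and 19% at 10%, 20%, 30% and 40% background. For 5% vs 15% it is about 85% alone and 54%, 36%, 25% and 19%.

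**6. The opposite case.** Suppose the drug raises two independent reactions in one class, each 5% vs 12%. Each alone has about 61% power. Pooled, the rates are 1 − 0.95² = 9.75% and 1 − 0.88² = 22.56%, with power about 88%. With 10% background they become 18.8% and 30.3%, and power is about 67%, still above a single reaction.

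**The case against.** Four objections have force, and each rules out a stronger reading.

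- **A reader might infer that the trial cannot say which reaction occurred or how severe it was.** The documents do not support this. The event log holds that detail, and 6.4 does not forbid descriptive tables from it. Serious events, suicidality and the number of discontinuations also have their own reporting. What is missing is pre-specification.
- **A reader might treat the seven items as direct reaction data from everyone assessed.** The Appendix says the questions had no timeframe and captured what participants currently believed and felt, so they do not measure incidence. Their wording and response format are not given. Nothing says that they went to every attendee, including participants already off medication. Table 1 also marks tolerability questions at week 12, while the Appendix places this set at weeks 4 and 8.
- **A reader might take the power loss as a property of this trial.** Every rate in it is assumed. Background may be low, since events came from open-ended prompts, and pooling can raise power, as step 6 shows. Nor does power justify a remedy that adds intervals rather than tests; the gain there is descriptive.
- **A reader might suppose that adverse events leading to discontinuation can simply be tabulated.** The Appendix's description of the event form names no field linking an event to stopping, and section 4.4 gives side-effects and no longer wanting to take part as example reasons within the same group of 56.

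Finally, section 6.7 refers to exploratory analyses in the protocol, which is not part of the text reviewed. The same section says that no SAP exists for them.

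**Conclusion.** The point stands for the SAP. The planned comparison of adverse events stops at System Organ Class, specific events and non-serious severity have no pre-specified summary by arm, and the expected-effect questions have no planned analysis. This follows from the text and rests on no assumption.

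The possible loss from masking is illustrative: from about 94% power to between 88% and 36% over 5% to 40% background, for assumed rates of 10% and 25%, independent background equal in both arms, and about 160 per arm. It applies when one reaction shares a class with unrelated events; it can reverse when several rise together. The efficacy analyses are unaffected. What the present plan leaves to later choice is which reactions are shown, how often they occurred and how severe they were.

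**What to change.** Keep the System Organ Class table. Before unblinding, add to section 6.4:

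1. The percentage of participants with each MedDRA preferred term occurring in at least 5% of either arm, by arm and by worst severity, with risk difference and 95% CI and no further tests. At 160 per arm the threshold is 8 participants (0.05 × 160).
2. A descriptive summary by arm of the seven expected-effect items at weeks 4 and 8, labelled as untimed ratings of current beliefs rather than incidence.
3. Numbers discontinuing medication by arm and recorded reason, with adverse events leading to discontinuation where the records allow.

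Also reconcile the listing of adverse events in section 5.4 with section 6.4, and the timing of the tolerability questions in Table 1 with the Appendix.

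The cost is SAP wording and extra tables from data already collected. If events were coded only to System Organ Class, item 1 needs the logged descriptions coded to preferred term. The downside is more descriptive comparisons, some of which will differ by chance; giving intervals without tests limits over-reading.
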